### Implementation strategies

Semi-structured qualitative interviews of patients and clinicians will explore the attitudes and opinions to understand the experiences of those involved in *DPYD/UGT1A1* PGx screening. Forty representatives from patient and clinician groups will be selected at random. These data will be used to optimise the PGx screening process and provide tailored support and educational resources where required. Interviews with patients will be conducted following enrolment, genotyping and at least the first FP cycle. Clinicians will be contacted throughout the trial. Interviews will be recorded, de-identified and securely stored on password-protected university servers.

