**Fig. 1 Fig1:**
[figure not shown]
Metabolic Pathway of Fluoropyrimidines, adapted from White [8]. Legend: * Fluoropyrimidine chemotherapeutic agents, ^ Genes. Enzymes: CES; carboxyl esterase, CDA; cytodine deaminsae, TP; thymidine phosphorylase, TS; thymidylate synthase, DPD; dihydropyrimidine dehydrogenase, DHP; dihydropyrimidinase, B-UP; beta-ureidopropionase. Metabolites: 5’dFCR; 5’-deoxyfluorocytidine riboside, 5’dFUR; 5’-deoxyfluorouridine, FUH2; dihydrofluorouracil, FUPA; fluoro-beta-ureidopropionate, FBAL; fluoro-beta-alanine, FUMP; fluorouridine monophosphate, FUDP; fluorouridine diphosphate, FUTP; fluorouridine triphosphate, FUDR; fluorodeoxyuridine, FdUMP; fluorodeoxyuridine monophosphate, FdUDP; fluorodeoxyuridine diphosphate, FdUTP; fluorodeoxyuridine triphosphate, dUMP; deoxyuridine monophosphate, dTMP; deoxythymidine monophosphate. Genes: DPYD encodes DPD, TYMS encodes TS

Throughout Europe, four clinically significant *DPYD* variants are increasingly screened prior to administration of FP agents, endorsed by the European Medicines Agency and local government bodies [11–16]. People found to carry *DPYD* variants (c.1905 + 1G > A, (*DPYD* *2A), c.2846A > T, c.1679 T > G and c.1236G > A/HapB3), have decreased function of their alleles to make DPD enzyme, resulting in DPD deficiency and FP toxicity when standard FP doses are administered [17, 18] (Table 1). Approximately 8% of the European-Caucasian population carry one of these four variants, and other variants of significance in non-Caucasian populations are emerging and are likely to become incorporated in standard screening panels as supporting data expands [19, 20]. There is a limited understanding of *DPYD* expression in Aboriginal and Torres Strait Islander communities, although a small genomic study from a single indigenous population in the Tiwi Islands suggests that *DPYD* and *UGT1A1* expression differs from Caucasian data [21, 22].

**Table 1 Tab1:** Clinically significant DPYD variants: variant allele frequency, DPD enzyme function, and relative-risk of FP-related toxicity

*DPYD* variant (rs number)	Variant Allele Frequency^a^ [3]	Allele function	Relative Risk of Toxicity at standard FP dose, (95% CI) [17, 18]
c.1905 + 1G > A, *DPYD**2A (rs3918290)	0.9–1.5%	No function	2.85 (1.75–4.62)
c.1679 T > G (rs55886062)	0.1–0.2%	No function	4.40 (2.08–9.30)
c.2846A > T (rs67376798)	1.1–1.5%	Partial function	3.02 (2.22–4.10)

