### Implementation sub-study intervention

Qualitative interviews will be conducted with a convenience sample of 20 to 40 patients and clinicians involved in PGx screening, with the sample size dependent on achieving sufficient breadth and depth as is favoured over saturation in this methodology [29]. Interviews with patients will be conducted following enrolment, genotyping and at least first cycle of chemotherapy. Clinicians will be contacted throughout the trial. This will be decided by the research team through discussions parallel to recruitment and data collection. Participants will be asked to complete semi-structured qualitative interviews over the telephone or teleconferencing which will be up to 45 min in length. Patient interviews will explore the degree to which people offered genotyping were aware of and understood the purpose of genetic testing and dose-personalisation in the trial, experiences of *DPYD* variant carriers who received *DPYD* genotype-guided dose-personalisation, including information needs around*,* and lived-experiences of dose-personalisation throughout treatment. Clinician interviews will explore the experiences of using *DPYD* PGx-guided dose-personalisation, including reasons for adjusting/not adjusting the dose, intention to continue using *DPYD* PGx-guided dose-personalisation, and barriers and facilitators to this prescribing method.

Interview recordings will be transcribed, deidentified and imported into a qualitative data analysis software package for analysis. Interview and focus group transcripts will be deidentified prior to analysis. Only members of the research team who are not involved in patient care will be involved in the analysis. Reflexive thematic analysis will be conducted to explore the commonalities and dissimilarities within and across the data, and reflexive practice will be employed to acknowledge and account for any subjectivities (bias) in the data analysis [30]. These findings will be used to optimise the PGx screening process and provide tailored support and educational resources.

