#### Sample size determination

This project intends to capture and test most feasibly large cohort of patients based on average clinical volume and anticipated number of patients that are eligible for testing across all study sites. Approximately 17000 patients are treated with FP per annum, resulting in > 30,000 potentially eligible patients across just 2 years of recruitment. As such, 5000 subjects in this study would require a recruitment capacity of < 15%. Our participating sites provide care for > 30% of Australians with cancer.

Based on expected frequency of *DPYD* variant alleles (~ 4% as a conservative estimate), testing *N* = 5000 patients will result in ~ 200 patients with actionable genotypes. Toxicity in these patients will be compared to historical datasets (Table 4). Assuming toxicity decreases to 35% in those receiving PGx- guided dosing, *N* = 70/arm will provide 80% power to detect a significant improvement in FP-related toxicity at the 5% level.

**Table 4 Tab4:** Populations for analysis

**Analysis Population**	**Description**
Testing Set	All patients who are eligible for recruitment and undergo* DPYD* genotyping
*DPYD *Set	Patients in this study who are found to carry a *DPYD *variant. Comparator groups include: 1) retrospective review of FP toxicity in *n*=500 patients who were treated without genotyping 2) contemporaneous cases without *DPYD *variants treated with standard doses 3) contemporaneous cases of *DPYD *variant carriers who do not receive dose-adjustment, and 4) *DPYD* variant carriers in European cohorts who were treated with dose reduction

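### The protocol gives conflicting selection rules for the same interviews, and simple random selection would reach only about one to three DPYD variant carriers

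*Protocol article*

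**What the plan says.** The interviews appear in two sections of the protocol article.

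- **Implementation sub-study intervention:** "Qualitative interviews will be conducted with a convenience sample of 20 to 40 patients and clinicians involved in PGx screening", and the number is left open, "with the sample size dependent on achieving sufficient breadth and depth as is favoured over saturation in this methodology". The research team decides as recruitment and data collection go on. Among the topics for patients, this section lists "experiences of *DPYD* variant carriers who received *DPYD* genotype-guided dose-personalisation", next to awareness and understanding of testing among everyone offered it.
- **Implementation strategies:** "Forty representatives from patient and clinician groups will be selected at random". No sampling frame, stratification or patient/clinician split is given.

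Two figures elsewhere set the share of carriers among patients. Sample size determination plans on a low value: "Based on expected frequency of *DPYD* variant alleles (~ 4% as a conservative estimate". The Background gives a higher one: "Approximately 8% of the European-Caucasian population carry one of these four variants".

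Table 2 places the work on enablers and barriers, with patient and clinician interviews as part of its endpoint, under the primary objectives.

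**The concern.** A convenience sample and a random sample are different designs, and a number judged during data collection is a different rule from a number fixed at forty. A site or analyst cannot follow both sections.

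The choice also has a practical consequence. Only carriers whose dose was adjusted can describe what genotype-guided dosing was like for them, and carriers are a small minority of enrolled patients. A simple random draw of a few dozen people would contain very few of them. One of the topics the sub-study sets itself would then rest on a handful of interviews, or on none.

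**Working it through.** **1. Are these the same interviews?** Yes. Both sections describe semi-structured interviews with patients and clinicians. Both place patient interviews after enrolment, genotyping and at least one cycle, contact clinicians throughout the trial, and use the results to improve the screening process and tailor support and education.

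**2. Where do the rules differ?**
- Method: convenience in one section, random in the other. These cannot be reconciled.
- Sizing: judged by breadth and depth in one, fixed in the other. These also conflict.
- Number: 40 is the upper end of 20 to 40. The figures themselves are compatible.

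**3. Inputs for the carrier count**
- Carrier prevalence p: 4% (Sample size determination) and 8% (Background).
- Patients n among the forty interviewees: not stated. Assumed 20 to 40; 40 would leave no clinicians, so it is the most favourable limit.
- Selection: assumed simple and unstratified across all enrolled patients.

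**4. The plan's own figure.** 5000 × 0.04 = 200, which matches the roughly 200 patients with actionable genotypes stated in Sample size determination. The 4% therefore acts as a share of patients.

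**5. Carriers interviewed under simple random selection.** With X ~ Binomial(n, p), the expected number is n × p and the chance of none is (1 − p)^n.

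| Patients n | p | Expected carriers | Chance of none | Chance of five or more |
|---|---|---|---|---|
| 20 | 4% | 20 × 0.04 = 0.8 | 0.96^20 = 44% | 0.1% |
| 40 | 4% | 40 × 0.04 = 1.6 | 0.96^40 = 20% | 2% |
| 20 | 8% | 20 × 0.08 = 1.6 | 0.92^20 = 19% | 2% |
| 40 | 8% | 40 × 0.08 = 3.2 | 0.92^40 = 4% | 21% |

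If only 10 of the forty were patients, the expectation would fall to 0.4 at 4% and 0.8 at 8%.

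**6. Carriers versus dose-adjusted carriers.** The table counts all carriers. The protocol also names carriers who do not receive dose adjustment as a comparator group, so the number who can speak about dose-personalisation may be somewhat lower.

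**The case against.** The strongest reply concerns how far the contradiction reaches.

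- A reader might infer that the aim on carriers' experience cannot be met. The documents do not support that. The aim is stated only in the section that uses convenience sampling, and under that rule the team could approach carriers from the roughly 200 expected. The shortfall arises only if the section on random selection governs and the draw is unstratified, which the protocol does not say.
- A reader might also take one carrier as the expected yield. That rests on the 4% value, which the protocol itself calls conservative, and on an assumed patient/clinician split. Across the stated prevalences and 20 to 40 patients, about one to three is the fair range. Even with 20 patients at 4%, at least one carrier is more likely than not (100% − 44% = 56%).
- Carriers' experience is one of several topics. Clinician interviews separately cover reasons for adjusting or not adjusting doses. Few carrier interviews would thin one topic; they would not empty the objective on enablers and barriers.
- Quotas and sampling frames are details that an article may leave to the full protocol, so the lack of a carrier quota under the convenience rule is not in itself an error.

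All four points stand and limit the finding. They do not remove it: the article states two selection methods for one set of interviews, and one of them serves a stated topic poorly.

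**Conclusion.** The protocol contradicts itself on how interviewees are selected and on how the number is settled. This needs no assumption.

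The consequence is conditional. If random selection is followed as simple unstratified sampling, with 20 to 40 patients among the forty, about one to three carriers are expected (0.8 to 3.2), and the chance of none runs from 44% at the least favourable combination to 4% at the most favourable. Five or more carriers would be unlikely in every case shown (at most 21%). That is too few to explore how experiences of dose-personalisation agree and differ.

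The point is confined to the interview sub-study. It is worth correcting because the interviews feed an objective listed as primary and the correction is cheap.

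**What to change.** In Implementation strategies, delete the words on random selection and the fixed count of forty. State one rule in both sections: 20 to 40 interviews in total, sized by breadth and depth, with purposive inclusion of dose-adjusted variant carriers alongside non-carrier patients and clinicians.

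This changes about two sentences and adds no interviews. With roughly 200 carriers expected in the study, there are enough to approach. The small downside is that fewer interviews will be held with non-carrier patients.

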### Translational research

A portion of patients will develop ≥ G3 toxicities without being carriers of one of the genotyped *DPYD* variants, suggesting they either carry different clinically significant *DPYD* variant(s) or other genetic/epigenetic drivers of FP toxicity yet to be identified. We will conduct additional gene sequencing on bio-banked specimens to determine other genetic influences on FP toxicity. Furthermore, we will be able to provide further data regarding the limitations of linkage disequilibrium of c.1236G > A and HapB3 haplotype (c.1129-5923C > G, rs75017182) as described by Turner et al. [32]. This information will ideally help to tailor a PGx panel specific to our diverse Australian population to assist with identifying maximum numbers of patients at risk of toxicity prior to first FP exposure.

## Discussion

Although there have been many advances within pharmaceutical prescribing in oncology, fluoropyrimidines continue to form the backbone of many chemotherapy regimens used across a variety of solid organ cancers. With the rise of personalised and precision medicine it is imperative that the oncology community strive to make cancer therapies more tolerable for patients to facilitate adherence and efficacy, whilst considering the cost-effectiveness of these decisions on the wider health system. The implementation of upfront *DPYD* genotyping has been clinically and economically successful in countries where standardisation has been implemented [17, 25, 28].

Despite the incidence of avoidable serious FP-related toxicities and deaths, Australia is yet to adopt a standardised approach to minimise these complications. In additional to the perceived barriers held by clinical stakeholders, the expansive geographical reach of testing facilities and health services poses a unique barrier to the development of readily accessible PGx screening services with short TATs.

This research program intends to support the large-scale feasibility, safety and cost-effectiveness of upfront *DPYD* (and eventually *UGT1A1*) genotyping for people in Australia affected by cancer. Standardisation of PGx screening services and procedures across centres throughout multiple Australian states will help to create geographically local ‘hubs’ where genotyping can be offered and initiated in a time and cost-effective manner. Through the incorporation of implementation research strategies and patient and clinician feedback, this project intends to introduce a successful program that will maintain sustainability beyond the clinical trial environment. This program will create an accessible and equitable nation-wide PGx screening service available to all patients intended to receive FP chemotherapies. By improving personalised prescribing and limiting severe treatment-induced toxicity, patients will be more likely to complete intended treatment protocols and achieve better cancer related outcomes. Importantly, it will also serve as an Australian prototype not only for other gene/drug pairs implicated in oncology, but for other PGx screening programs across other health disciplines.

In addition, this study will develop an important database of patients who, despite “functional” *DPYD* genotypes, go on to develop ≥ G3 FP-induced toxicities. Further genomic analyses of these patients will help to uncover additional causative *DPYD* variants that may need to be considered for inclusion in a *DPYD* screening panel that is tailored to the Australian population. This includes understanding patterns of *DPYD* and *UGT1A1* expression in our Indigenous communities and working toward an inclusive pharmacogenomic screening panel. There may also be additional genetic and epigenetic factors identified within this Australian cohort that can be factored into the personalised prescribing of FP chemotherapies in the future.

## Data Availability

No datasets were generated or analysed during the current study.

## Abbreviations

5-FU: 5-Fluorouracil
DFS: Disease-free survival
DPD: Dihydropyrimidine dehydrogenase (enzyme)
DPYD: Dihydropyrimidine dehydrogenase (gene)
FP: Fluoropyrimidine
ICU: Intensive care unit
OS: Overall survival
PFS: Progression-free survival
PGx: Pharmacogenomic
TAT: Turnaround-time
UGT1A1: Uridine-diphosphate-glucuronosyltransferase family 1
